### Intervention development and planning

Two steering groups will be established at each company. One is a strategic steering group consisting of a managerial group (often the managerial team) responsible for long term adaptation and evaluation of the usefulness of PIPPI, and the other is a project steering group responsible for monitoring and supporting the day to day activities of PIPPI. The steering group will manage the overall intervention process and ensure intervention progress at all levels of the organization throughout the project period. The steering group will (a) support data collection for effect and process evaluation, (b) discuss and monitor the screening process and developed action plans, (c) facilitate participation in intervention activities, (d) follow-up on progress, (e) reflect on the factors which will facilitate or hinder the progress of intervention, (f) discuss the evaluation of organizational resources and the corresponding action plan and (g) develop a communication strategy to ensure distribution of proper and timely information to the participating workers, managers and support systems.

The individual (I), group (G), leader (L), and organizational (O) levels of the workplace, referred to as IGLO [48], will be actively involved in the intervention activities. It signifies an approach that seeks to coordinate and integrate intervention activities at various levels of the organization. The aim of this approach is to achieve a thorough implementation and support throughout the organization. The specific intervention activities are listed below according to the level of the organization involved.

#### Group level

At the work team level, workshops are conducted to map the work environment, create action plans, and monitor the implementation of these action plans [48]. The three designated workshops are carried out by the work team together with a consultant or person from the research group using a participatory approach. A member of the research group will be present at all workshops to observe the process, and all workshops will be documented with audio recordings.

The first workshop is a collaborative screening process labelled a “Visual Mapping Workshop” (VMW) based on cognitive mapping interview techniques [49]. The VMW will focus on producing a visualization of the factors affecting the team member’s ability to work, i.e. positive and negatives aspects of work (based on the job demands-resources model [50]. Furthermore the workers are given time to construct an individual map of the factors affecting their work ability, both positively and negatively.

At the subsequent Action Planning Workshop (APW), the participants will revisit the visual map developed at VMW and use it to create action plans aiming to restore or improve the balance between demands and resources of the workers. The consultant will support the participants in the APW in making action plans that list the goals and responsibilities of individual team members and the time frame of the developed action plans. Likewise, the cost-effectiveness of all action plans are to be discussed and evaluated in a structured process focusing on their effectiveness (how many workers will be affected), and scale of effect (small-large effect) with respect to productivity, wellbeing and product quality, and their expected costs (e.g. working hours used, cost of modifying the production, or prize of new equipment). Subsequently, the developed action plans are prioritized based on their evaluated cost-effectiveness.

It will be emphasized that, in cases where there is no need for approval from senior management level or additional funding to the developed action plans, they should be implemented in the context of the work team. However, when the developed action plans involve large-scale organizational changes or additional funding, information of the action plan will be carried back to the steering group and discussed for being implemented.

The last workshop is a follow-up workshop (FUW), where the implementation of the previously developed action plans is assessed. There are clear recommendations in the occupational health psychology literature to support the implementation process, as studies have shown that the implementation conducted by the workers and line managers is often a weak point in organizational interventions [51,52]. To address this weakness, the FUW provides an opportunity for the line manager and employees to discuss the action plans with a process consultant provided by the research team.

Between the APW and FUW, sufficient time will be provided for employees and line managers to implement the proposed action plans, evaluate them, and if necessary modify or develop new action plans.

#### Leader level

At the leader level (where PIPPI will include health and safety representatives as experts on work environment issues), a one-day Ambassador Workshop (AW) will be conducted at each participating company for line managers, union and health and safety representatives. The objective of the workshops is to provide them the sufficient information and skills to take on the role of ambassador for the intervention and help the workers understand and gain access to information about the intervention. Participants in the workshops are trained to facilitate the implementation of developed action plans. Furthermore, the line managers will be trained to take a central role in the participatory process at the team and individual level (described below) as they are to offer individual work ability talks with each employee, as a supplement to the activities on the group level.

The AW includes (a) information about central guiding elements of the intervention such as participation, the demands-resources model, and the IGLO concept, (b) discussions about the expectations to the intervention as well as workers’ readiness for change, and (c) discussions regarding their roles supporting the intervention process. The AW will ensure that the line managers, union and health and safety representatives understand the overall aim of the intervention, the background for the PIPPI project, and requirements for a participatory approach. The discussions will facilitate development of common goals for the intervention, individual goals regarding their individual leadership capabilities and functioning of their work teams.

The AW will be supplemented with Learning Workshops (LWs) for the same group of line managers, union and health and safety representatives. The aim of the LWs is to discuss how they can support the implementation of action plans, and enable exchange of experiences between the participants about the progress of the intervention and the challenges faced along the way. The LW will be conducted after the first year of the intervention activities (described below).

#### Individual level

On a voluntary basis, an individual visual mapping sessions between interested employees and their line managers will be arranged. In these sessions, the principles of the first two workshops (VMW and APW) will be used at an individual level. The line manager will ask workers to individually identify key resources and demands in their work environment currently limiting or enhancing their work ability. This will provide the worker and the team leader with an overview of both the demands that could be modified and the resources that could be promoted in order to improve the work ability and reduce need for recovery for the worker. The session will result in the worker and team leader together developing future new action plans to address the specific elements leading to higher need for recovery and limiting the work ability of the individual worker if the workers wished it.

#### Organizational level

The intervention seeks to use existing organizational resources and facilities as well as the existing health and safety initiatives at the workplaces to facilitate various workshops and implementation of the intervention. An audit will be carried out aiming to map the organizational resources related to worker’s health and the work environment, as well as their current functioning [48]. Relevant workers in the organizational support systems as well as a representative sample of health and safety worker representatives will be interviewed and the formal and informal resources will be mapped, explained and evaluated. Utilizing a snowball sampling approach, each representative will also be asked for additional functions relevant for inclusion. Further interviews will be conducted with employees and managers regarding the use and function of these resources. Furthermore, existing written material related to the different functions and resources will also be collected from the workplace. A report will then be produced, summarizing the aforementioned resources as well as the perceptions about their effectiveness throughout the organization. The report will then be discussed in meetings with the project group and in the steering group. Subsequently, the additional action plans will be produced for the intervention group based on the results of the audit of organizational resources (ORA).

### Implementation of the intervention

For implementation of the action plans, the workplace will be provided with visual boards based on lean manufacturing also known as kaizen boards [53,54]. The boards can be used by the work teams as aids for discussing the progress of the action plans. In case the workplace does not already use similar systems, the workers will be instructed in how to use them. The visual boards contain areas for listing action plans currently being implemented by the team, new action plans, and details about the roles and responsibilities of individual employees or managers in implementing respective action plan. The board also allows easy charting of the progress of activities and supporting the discussion of action plans at regular team meetings. Kaizen boards follow a PDCA cycle (i.e. plan, do, check and act) in which the workers propose courses of action, implement them, evaluate their effectiveness and make adjustments to increase the efficacy of the courses of action [53]. The progress of the intervention will be discussed in the team meetings, commonly occurring at least every month, and on bi-weekly workers’ existing meetings where the teams are to briefly discuss the progress of the action plans.

The visual mapping developed at the team level will be analyzed and an overview of commonly mentioned demands and resources will be provided to the steering committee. Thus, if the workers indicate problems with the current systems and initiatives that were not identified during the ORA process, these problems can still be acted upon at a higher level than just the team, which are often unable to make decisions affecting overall workplace policies.

Another strategy of implementation is that the aid of an experienced ergonomic consultant will be available to the teams. Three hours of consultant assistance per work team will be allotted as part of the intervention, but the workplace can also bring in their own internal consultants or relevant persons of competence (e.g. production planners, machine experts) on a case-by-case basis if deemed relevant.

### Evaluation of the intervention

The evaluation framework of the intervention will comprise a comprehensive quantitative effect evaluation as well as a thorough process evaluation drawing on both quantitative and qualitative sources, i.e. a mixed methods approach.

#### Effect evaluation

The primary outcome of this study is the need for recovery and work ability [23,55]. Secondary outcomes are work demands and resources [23,56], and productivity [23]. The conceptual model to improve upon these outcomes is illustrated in Figure 2.

**Figure 2 Fig2:**
[figure not shown]
**Conceptual model for improving the need for recovery and work ability of workers.** Each strand of the intervention either generates action plans to improve the balance between work demands and resources, or assists the implementation of developed action plans. The improved balance between work demands and resources from implementation of the action plans is considered to improve the primary outcomes of this study.

#### Process evaluation

The quantitative-qualitative process evaluation framework at IGLO levels utilized in this study is inspired by Nielsen and Abildgaard [51]. The objective of the process evaluation is to identify the working mechanism of change based on four categories: *Organizational actors* or drivers of change which includes all key stakeholders (employees and management supporting intervention) who may influence the intervention process and therefore the intervention outcomes, *mental models* which includes cognitive appraisal of the organization, working conditions and the intervention program and its activities [57] that can help explain the behaviors of the organizational actors, *contextual* factors which hinders or facilitates intervention activities, and *interventions design and process*. Data will be collected at different levels of the organization to address specific issues and elements related to initiation of the intervention, development and implementation of intervention activities, identification of drivers of change, participatory approach involving the employees, senior management support, role of middle management and consultants, information and communication strategy of the intervention, screening, action planning, omnibus, discrete and contextual factors and workers’ mental models of the intervention and their work situation. Case study analyses [58,59] of the working mechanisms of the intervention are planned to be conducted based on a narrative approach to study organizational processes [60,61]. Furthermore, process data are planned to be used descriptively to document the degree of implementation in a mixed methods design. This allows us to evaluate if the intervention has been conducted as planned, and to investigate associations between process data and effects on the primary and secondary outcomes. The extensive process data collection using multiple data sources is preformed to ensure that potential changes in the companies or deviations from the planned intervention are documented thoroughly. It will hence be possible on the basis of a thoroughly pre-planned and standardized qualitative and quantitative process evaluation to conduct analyses on these elements.

### Data collection

The data from all IGLO levels will be collected via four methods: questionnaires, interviews, observations, and organizational records (Figure 3).

**Figure 3 Fig3:**
[figure not shown]
**Data collection for effect and process evaluation.** The data for process evaluation will be collected via (a) observation and audio recordings made during all main intervention activities, (b) questionnaires distributed to all team leaders, (c) various organizational documents such as evaluation forms from activities and meeting minutes collected during the course of intervention, and (d) interviews conducted at different levels of organization (example. health and safety representatives, human resources personnel, steering group members, and line managers and workers from both the intervention and control group). For collecting information for both effect and process evaluation, a main questionnaire at T0, T1 and T2 will be used.

The main questionnaire will consist of questions covering the primary and secondary outcomes, and process evaluation. Need for recovery will be determined using 9 items (eg. “how often do you have difficulties to relax after a workday”). The five responses categories are: 0 = never, 1 = rarely, 2 = some of the time, 3 = most of the time, and 4 = always. The need for recovery index will be composed based on the mean of all items. Work ability will be determined via the single work ability item (i.e. rating of the current work ability compared with the lifetime best) with response ranging from 0 (“unable to work”) to 10 (“work ability at its best) [62]. Besides the main questionnaire, need for recovery and work ability items are also included in a short email questionnaire which will be responded to by the participants two and four months prior to the follow-up main questionnaire. Process evaluation questionnaire items will be included in the follow-up questionnaire and will be based on scales and items from Randall and colleagues [63] and Nielsen and colleagues [64], adapted to fit the intervention context of industrial production (sample items include “my immediate manager was positive about the implementation of PIPPI” and “the project had led to sustainable changes in their workplace”). Data for process evaluation will be collected via audio recording of all group level workshops supplemented with observations of the workshop by a member of the research team adhering to a standardized set of instructions focusing on non-verbal aspects (i.e. elements that are not captured on the audio recording). Organizational data (action plans, meeting minutes etc.) are collected and semi structured interviews [65] are conducted in all teams using a standardized interview guide. Interviews will be conducted shortly prior to the effect evaluation questionnaire.

The work demands such as duration of lifting and carrying, pushing and pulling, physical exertion at work, duration spent in arm at or above shoulder, back bending forward and the resources such as physical fitness and strength will be measured using questions from a Danish national survey questionnaire [66]. Productivity at work will be measured using a validated single item ‘how would you rate your productivity at work’ in the last month, with responses ranging from 0 (worst) to 10 (best productivity). Psychosocial demands and resources will be measured using the WHO5 well-being index (5 items, sample item. during the last 4 weeks I have felt calm and relaxed) and the mental health subscale from the SF-36 questionnaire (3 items, sample item. during the last 4 weeks have you been very nervous) [67] both using 6 response categories ranging from “all the time” to “at no time”*.*

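### The psychosocial part of the demands-and-resources outcome is measured by well-being and mental-health scales, so the randomised comparison cannot show whether psychosocial work demands or work resources changed

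*Protocol article*

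**What the plan says.** Under Effect evaluation the protocol states: "Secondary outcomes are work demands and resources [23,56], and productivity [23"]. Data collection then says how this outcome is measured.

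- **Physical part.** The sentence opens "The work demands such as duration of lifting and carrying, pushing and pulling, physical exertion at work" and goes on to working postures. Fitness and strength are given as examples of resources. All of these come from a Danish national survey questionnaire.
- **Psychosocial part.** "Psychosocial demands and resources will be measured using the WHO5 well-being index" (5 items), and "the mental health subscale from the SF-36 questionnaire (3 items, sample item. during the last 4 weeks have you been very nervous").

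The legend to Figure 2 gives demands and resources their role in the programme theory: "The improved balance between work demands and resources from implementation of the action plans is considered to improve the primary outcomes of this study". The Statistics section applies the same mixed-model comparison of the two groups, from T0 to T1, to primary and secondary outcomes alike.

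**The concern.** A demand or a resource at work is a condition that the worker meets, such as pace, influence or support. A well-being or mental-health scale records the worker's state. The protocol uses the second kind of instrument under the name of the first.

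The stake is what may be concluded. The intervention is described as both physical and psychosocial, and changed demands and resources are the route by which it is meant to work. If the scales are analysed under their present label, a group difference in well-being would be reported as a change in psychosocial demands and resources, which is a different finding. If there is no difference, the report might say that psychosocial conditions did not change, and the data would not support that either.

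**Working it through.** No figure in the plan bears on this, so the check sets the statements side by side.

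**1. Is the psychosocial measurement closed or open?** The physical list is introduced by examples and is therefore open. The psychosocial sentence names two instruments and gives item counts, a sample item for each and a response format. It signals nothing further. This is a stated choice of measure and not a detail left for later.

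**2. What do the instruments ask?** The item count is 5 + 3 = 8, of which 2 are printed.

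| Scale | Items | Printed item | Refers to work? |
|---|---|---|---|
| WHO5 well-being index | 5 | "during the last 4 weeks I have felt calm and relaxed" | No |
| SF-36 mental health subscale | 3 | "during the last 4 weeks have you been very nervous" | No |

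Neither of the 2 printed items mentions work. The other 8 − 2 = 6 are judged only by the scale names, which are those of well-being and mental health.

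**3. How does the physical side compare?** Lifting, carrying, pushing and pulling are exposures at work, so that side has items that measure demands. The psychosocial side has no counterpart.

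**4. Does another quantitative measure fill the gap?** The article describes these other questionnaire contents:

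- need for recovery (9 items) and work ability (1 item), which are the primary outcomes;
- productivity (1 item);
- process items in the follow-up questionnaire, with samples about the manager's attitude to the project and lasting change at the workplace;
- a short email questionnaire, for which only need for recovery and work ability are mentioned.

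None is presented as a measure of psychosocial work demands or work resources at T0 and T1.

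**5. What could the T0–T1 comparison show?** A group difference on the WHO5 or the SF-36 subscale would be evidence about well-being or mental health. It could arise with psychosocial work conditions changed or unchanged, for example through physical improvements. The absence of a difference would likewise be compatible with changed or unchanged conditions. Neither result answers whether psychosocial demands or resources at work moved.

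**The case against.** Several counter-arguments have weight.

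- **The outcome is broader than its psychosocial part.** Effect evaluation names work demands and resources; the psychosocial wording appears only under Data collection. This stands. A reader might infer that the whole secondary outcome is unmeasured, but the physical part has suitable items.
- **Well-being may be a personal resource.** The protocol counts fitness and strength as resources, and the definition of work ability quoted in the Background mentions mental resources. This stands for personal resources. It covers neither psychosocial demands, which the same sentence claims to measure, nor resources at work.
- **The process evaluation also collects information.** Visual maps, action plans and interviews with workers from both groups can describe psychosocial conditions. This stands, so it would be too strong to say that the trial can learn nothing about them. These are process data, however, and the interviews are placed shortly before the effect questionnaire with no baseline counterpart stated. They do not supply the randomised comparison.
- **The causal position is not documented.** A reader might infer that the scales sit on the same side of the conceptual model as need for recovery, or that their correlation with it will be offered as proof of the mechanism. The documents do not support this. Figure 2 is not shown, and its legend does not place well-being or mental health. The article plans group comparisons, and associations between process data and effects. It plans no correlation of these scales with need for recovery and no mediation analysis.
- **The evidence on items is partial.** Six items are not printed, and the references cited for the outcome might contain a work-environment scale. This limits certainty. Still, the article says which instruments are used for the psychosocial part, and both are named for the worker's state.

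**Conclusion.** The point holds in a limited form. Two scales of well-being and mental health are labelled as measures of psychosocial demands and resources. As described, they measure no psychosocial work demand and no resource at work, and at most a personal resource. The quantitative T0–T1 comparison therefore cannot show whether psychosocial work demands or work resources changed.

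This rests on two assumptions: that the six unprinted items match the names of their scales, and that the main questionnaire holds no further psychosocial work scale, since none is named.

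Severity is minor. The primary hypothesis, the primary outcomes and the sample size are untouched. What changes is the label on one part of a secondary outcome and the conclusion it can carry.

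**What to change.** Report the WHO5 and the SF-36 subscale as two secondary outcomes, well-being and mental health, and state that no conclusion about psychosocial demands or resources at work will be drawn from them. This changes wording only and costs nothing.

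If a conclusion on psychosocial work conditions is wanted, add a short scale of psychosocial work demands and resources to the main questionnaire at T0, T1 and T2, and analyse it with the mixed model already planned. The cost is a few more items for respondents. The scale must be in place before baseline, because a missing T0 measurement cannot be recovered later. The article does not establish whether the baseline questionnaire can still be changed. If it cannot, relabelling is the remedy that remains, with the qualitative process data reported as such.
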